## Methods: participants, interventions, and outcomes

2

### Trial setting

2.1

The study will be conducted at the Regional Cancer Centre, Adyar, Chennai, India, over a period of 12 months.

### Trial design

2.2

This study is designed as a superiority, phase II, randomised controlled, open-label, two-arm parallel-group trial comparing participants with RIOM receiving a Siddha regimen as an adjunct to SOC with those receiving SOC alone. The primary endpoint of the study is the reduction in the incidence of severe RIOM, which will be assessed using RTOG grading scale during the course of radiotherapy and again at six weeks after completion of treatment. Participants will be randomly assigned in a 1:1 ratio (Siddha + SOC Vs SOC alone) using variable block sizes to maintain balance between groups, and allocation concealment will be ensured through the sequentially numbered, opaque, sealed envelope (SNOSE) technique. Subgroup analyses are also planned according to treatment modality, including radiotherapy alone, concurrent chemoradiotherapy, and post-operative radiotherapy. Since the study is designed as an open-label trial, centralised assessment of outcomes will be performed wherever possible to reduce the risk of assessment bias.

### Eligibility criteria

2.3

#### Inclusion criteria

2.3.1

Participants aged 20–75 years of any gender, diagnosed with head and neck cancers involving the oral cavity and/or oropharynx and scheduled to undergo radiotherapy for a period of 4–7 weeks with a total radiation dose of 55–72 Gy, will be eligible for inclusion in the study. Only those who are willing to participate and are willing to provide written informed consent before the enrolment, will be included.

#### Exclusion criteria

2.3.2

Participants will be excluded if they have a known hypersensitivity to any ingredient of the Siddha formulation, have active oral infections not related to radiotherapy, or suffer from any severe systemic illness in the view of the investigator may make them unsuitable for participation. Individuals concurrently enroled in another clinical trial, those using dentures, and patients undergoing re-irradiation or palliative radiotherapy will also be excluded from the study.

#### Criteria for discontinuing or modifying allocated interventions

2.3.3

Participants may be withdrawn from the study prior to completion if they withdraw informed consent at any time without providing a reason, develop serious or intolerable adverse reactions, or experience worsening of RIOM or the emergence of other medical conditions requiring treatment that is incompatible with continued study participation. Participants may also be withdrawn in cases of repeated non-adherence to study procedures, scheduled visits, or the medication regimen, defined as less than 70% drug compliance despite counselling, or if they are unable to be contacted for scheduled assessments despite reasonable efforts.

### Interventions and comparator

2.4

#### Intervention description

2.4.1

Arm A will constitute the intervention group, in which participants will receive the Siddha regimen as an adjunct to SOC during the entire course of radiotherapy and the post-radiotherapy period. Participants will be assessed weekly throughout the study duration or until complete recovery from oral mucositis, whichever occurs earlier.

***Procurement of trial drugs:*** The interventional drugs will be procured from GMP certified manufacturers. TPC will be procured from TAMPCOL, Chennai and GV will be procured from IMPCOPS, Chennai.

***Method of drug administration:*** The Siddha intervention will consist of TPC mouthwash and topical application of GV, administered as follows. TPC mouthwash will be prepared using pre-measured teabags, each containing 2 g of TPC. Participants will be instructed to immerse one teabag in 60 mL of freshly boiled water and allow it to stay immersed for 10–15 min, until the solution cools to room temperature. The teabag will then be removed, and the resulting solution will be used immediately as a mouth rinse. Fresh preparation will be performed prior to each use. Then, participants will be instructed to rinse with 60 mL of the mouthwash at each time point, three times daily after meals, swishing for 30seconds and then spitting out the solution. The mouthwash regimen will commence on day0 (one day prior to initiation of radiotherapy) and will continue during radiation therapy and 6weeks post radiation therapy. In addition, GV will be administered at a dose of 10 g per day, applied topically within the oral cavity three times daily, following mouth rinsing. Depending on the clinical schedule, treatment may be initiated on the same day as radiotherapy in some participants.

All participants in Arm A will also receive SOC, which includes 0.15% benzydamine mouth rinse (15 mL for 30–40 s, six times daily), along with topical anaesthetics and anti-inflammatory gels in cases of oral mucositis of grade ≥ 2, as per the institutional protocol. To minimize potential interactions, a standardized administration schedule will be followed. In the intervention arm, 0.15% benzydamine mouth rinse will be used three times daily before meals and three times daily after GV application. TPC mouthwash will be administered at least 30 min after meals, followed by GV application after 10–15 min. Participants will avoid eating or drinking for 30 min after GV application, and adherence will be monitored throughout the study. Details of the investigational drugs and SOC, including dosage specifications, are presented in Table 1.

**Table 1 T1:** List of Siddha interventions and SOC with dose administration details.

S.No	Treatment category	Drug Name	Dose & Vehicle	Total duration
1	Siddha intervention	Thiripala chooranam	180 mL, mouth rinse 3 times per day in divided doses (60 mL per time)	10−13 weeks
2	Siddha intervention	Gungiliya vennai	10gm - 3 times per day in divided doses	10−13 weeks
3	SOC	0.15% benzydamine mouth rinse	15 mL - mouth rinse 6 times per day	10−13 weeks

#### Comparator description

2.4.2

Participants in Arm B will receive SOC alone for the management of RIOM, as described in the intervention arm. Additional topical anaesthetic and anti-inflammatory gels will be provided for oral mucositis of grade ≥ 2 in accordance with institutional protocol.

Assessments will be conducted weekly, in parallel with the intervention arm, until 6week post radiotherapy or until recovery, whichever occurs earlier. Treatment adherence will be monitored by the oral hygiene coordinator, staff nurse, and investigators, with family caregivers trained during the radiotherapy admission period to assist in monitoring during the post-radiotherapy phase. Trial interventions will be administered for 10–13 weeks, depending on the required radiation dose (Gy) based on tumour size and severity. Recovery will be defined as Grade 0 oral mucositis on both RTOG and WHO oral mucositis scales. All participants will receive radiotherapy using a linear accelerator (LINAC) with three-dimensional conformal radiotherapy (3DCRT) for a duration of 4–7 weeks, in accordance with institutional practice. Before initiation of radiotherapy, all participants will undergo a baseline oral examination and receive necessary dental care, wherever feasible, according to institutional standard dental care protocols. Standardized oral hygiene instructions will be provided and reinforced uniformly throughout the study period in both study arms.

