### Background and rationale

1.1

Head and neck cancer arises from the epithelial lining of the upper aerodigestive tract and represents the seventh most common malignancy worldwide (1). Radiotherapy, either alone or in combination with concurrent chemotherapy, remains a cornerstone in the management of these malignancies (2). However, these treatment strategies are commonly associated with wide range of oral complications, including oral mucositis, secondary infections, xerostomia, dysgeusia, pain and an increased risk of dental and periodontal diseases. These complications impair essential activities like eating, swallowing, speaking and thereby reducing quality of life of patients. In severe cases, they may lead to treatment interruptions, infections and compromised oncological outcomes (3, 4).

Among the complications, oral mucositis (OM) is one of the most dose limiting toxicity of cancer treatment and it is featured by inflammation and ulceration of oral mucosa, typically developing 5–7 days after the initiation of chemo and radiotherapy. Approximately 40% of head and neck cancer patients receiving chemotherapy alone develop OM, whereas 90%–100% patients receiving concurrent chemo-radiotherapy (5). Evidence from Indian clinical settings indicated that radiation-induced oral mucositis (RIOM) usually appears after a cumulative radiation dose of approximately 20Gy, becomes more widespread at around 30Gy, and reaches peak severity with Grade 3 reactions at cumulative doses of 66 – 70Gy (6).

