RTOG Oral Mucositis Scale	Grade 0	No change
	Grade 1	Irritation/ Mild pain not requiring analgesics
	Grade 2	Patchy mucositis with inflammatory serosanguinous discharge/ moderate pain requiring analgesics
	Grade 3	Confluent fibrinous mucositis/ severe pain requiring narcotic analgesics
	Grade 4	Ulceration, haemorrhage, or necrosis
WHO Oral Mucositis Scale	Grade 0	No oral mucositis
	Grade 1	Erythema and soreness
	Grade 2	Ulcers present & able to eat solid food
	Grade 3	Ulcers present& requires liquid diet due to mucositis
	Grade 4	Ulcers present; alimentation not possible due to mucositis
VAS for Oral Cavity Pain	0	No pain
	1–3	Mild pain
	4–6	Moderate pain
	7–10	Severe pain
WHO Three-Step Analgesic Ladder	Step 1	Mild pain; Non-opioid analgesics (paracetamol, NSAIDs) ± adjuvants
	Step 2	Mild to moderate pain; Weak opioids (e.g., codeine, tramadol) ± non-opioids and/or adjuvants
	Step 3	Moderate to severe pain; Strong opioids (e.g., morphine, fentanyl, oxycodone) ± non-opioids and/or adjuvants

To evaluate treatment response over time, the percentage distribution of grades/scores obtained from the four above mentioned scales will be assessed separately for each study arm at weekly intervals during study period. These assessments will help compare the severity of mucositis, recovery patterns, pain levels, and analgesic requirements between the two groups over the course of treatment and follow-up. Certain practical limitations may arise while applying the WHO oral mucositis scale in specific clinical situations. For example, some patients may already be receiving nutrition through a nasogastric (NG) tube due to tumour-related obstruction, poor nutritional status, or severe RIOM. In such cases, oral intake is restricted to liquids irrespective of the actual severity of mucositis, which could result in overestimation of the grade, such as categorizing the condition as Grade 3 despite the absence of corresponding clinical findings. To avoid such misclassification, these cases will be recorded as “Not Applicable” for WHO grading, along with proper justification in the study records.

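### The rule that ends weekly assessment at recovery does not require radiotherapy to be over, so one grade 0 reading in mid-course can end observation before the primary event

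*Protocol article*

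**What the plan says.** Two sections set the end of weekly assessment. For the Siddha arm, section 2.4.1 says: "Participants will be assessed weekly throughout the study duration or until complete recovery from oral mucositis, whichever occurs earlier". For the control arm, section 2.4.2 has assessments run "until 6week post radiotherapy or until recovery, whichever occurs earlier". Section 2.4.2 then gives the only definition of the term: "Recovery will be defined as Grade 0 oral mucositis on both RTOG and WHO oral mucositis scales". It does not mention the end of radiotherapy, an earlier grade of 1 or more, or the number of readings needed.

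Grade 0 on the WHO scale is "No oral mucositis" (Table 3), and RTOG grade 0 is likewise the absence of any change. That is also the state before mucositis begins. Observation starts before or at the start of treatment: "The mouthwash regimen will commence on day0 (one day prior to initiation of radiotherapy", with a same-day start allowed for some participants.

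On the time course, section 1.1 says that RIOM "usually appears after a cumulative radiation dose of approximately 20Gy" and "reaches peak severity with Grade 3 reactions at cumulative doses of 66 – 70Gy". Section 2.5 counts RTOG grade 3 or higher occurring at any point during radiotherapy or in the six weeks after it.

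**The concern.** The primary outcome is an ever/never event that, on the article's own account, is most likely late in radiotherapy. A rule that can end observation in the middle of radiotherapy can therefore remove a participant from view before the event. The article does not say how the missing later weeks would be handled. If such a participant is counted on the readings obtained, the result is 'no severe RIOM'.

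There is a smaller descriptive problem. Of the weekly grade distributions the article says: "These assessments will help compare the severity of mucositis, recovery patterns, pain levels, and analgesic requirements between the two groups". If grade 0 counts as recovery whatever came before it, a recovered label cannot separate participants who healed from those not yet affected or never affected.

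**Working it through.** **1. When the rule can be met, against the dose figures.** Inputs: total dose 55–72 Gy over 4–7 weeks (section 2.3.1); onset at about 20 Gy and peak at 66–70 Gy (section 1.1). Dose is assumed to be spread evenly over the weeks.

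- Dose per week = total dose / weeks. Lowest: 55/7 = 7.9 Gy. Highest: 72/4 = 18.0 Gy.
- Time to 20 Gy = 20 / weekly dose, which is 20/18.0 = 1.1 weeks to 20/7.86 = 2.5 weeks.
- In a 7-week course, cumulative dose at week 4 is 4 × 55/7 = 31.4 Gy to 4 × 72/7 = 41.1 Gy. That is past the onset figure and well short of 66 Gy. Participants with a total dose below 66 Gy never enter the 66–70 Gy range, but their highest cumulative dose still comes at the end of the course.

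**2. A record that meets the rule.** Take grade 1 at week 3, grade 0 on both scales at week 4 and grade 3 at week 7, in a 7-week course. The definition is met at week 4, after mucositis has been recorded, and the clauses in 2.4.1 and 2.4.2 then end assessment. The week 7 event falls inside the section 2.5 outcome window but would not be observed.

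**3. The other passages, side by side.**

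| Place | What it provides |
|---|---|
| 2.4.1, 2.4.2 | Weekly assessment ends at recovery if that comes first |
| 2.5 | Primary event counted through radiotherapy and six weeks after |
| Table 2 | RTOG at baseline, W1–W8 and W13; WHO scale every week; no exception for recovery |
| 4.1 | Weekly assessment for the whole of radiotherapy, then telephone follow-up to six weeks |
| 6.5 | Both arms followed for six further weeks, weekly by telephone |

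The first row cannot be applied together with the other four in a participant who reaches grade 0 early.

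**4. Illustration of size (all inputs assumed).** Let q be the chance that a true grade 1 is recorded as 0 on both scales at one visit. Suppose half of participants have one weekly visit at grade 1 and half have two, that higher grades are never read as 0, and that staff require an earlier recorded grade of 1 or more before calling anyone recovered. A false stop then needs two grade 1 visits, the first read correctly and the second read as 0:

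P(false stop) = 0.5 × q × (1 − q)

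| q | P(false stop) |
|---|---|
| 5% | 0.5 × 0.05 × 0.95 = 2.4% |
| 10% | 0.5 × 0.10 × 0.90 = 4.5% |
| 20% | 0.5 × 0.20 × 0.80 = 8.0% |
| 30% | 0.5 × 0.30 × 0.70 = 10.5% |

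If false stopping is unrelated to later severity, the same share of severe events is lost. The 43.6% severe rate under benzydamine cited in section 2.7 would then be observed as 43.6 × (1 − 0.024) = 42.6% to 43.6 × (1 − 0.105) = 39.0%.

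If an earlier recorded grade is not required, a misreading at any grade 1 visit suffices. At q = 5% the figure becomes 0.5 × 0.05 + 0.5 × (1 − 0.95²) = 7.4%, before counting anyone who read 0 before onset.

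**The case against.** The strongest reply is that no trained assessor would apply the rule in this way. Section 2.4.1 speaks of complete recovery from oral mucositis, and one does not recover from a condition not yet present. Table 2 and sections 2.5, 4.1 and 6.5 all describe continued observation, and section 4.2 describes close in-patient follow-up during radiotherapy. If Table 2 is followed for everyone, the definition loses no primary event. Recovery is not a listed outcome either, and complete weekly grades would themselves show who was never affected and who healed.

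Much of this stands, and it disposes of a stronger reading. A reader might infer that nearly every participant meets the rule at week 1, since every eligible schedule is then below 20 Gy. The wording allows that, but the documents do not support it as an expectation: the ordinary sense of recovery excludes it, and section 1.1 also gives onset at 5–7 days, so some participants may already be above grade 0 by week 1.

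The reply does not reach the grade 1 then grade 0 sequence, which satisfies even the ordinary sense of recovery. Nor do Table 2 and the other sections override the two stopping clauses; they contradict them. A condensed article may leave detail to the full protocol, but this is a stated rule that gives the wrong result, not an omitted detail.

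**Conclusion.** The point holds in limited form. As written, the assessment rule can be met during radiotherapy by a participant with earlier mild mucositis and one grade 0 reading, and a later primary event could then go unrecorded. The rule also contradicts the article's own schedule and outcome window. Both follow from the text alone.

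The size does not. Under the assumed misreading rates of 5% to 30% at grade 1, roughly 2% to 11% of participants would stop falsely. That range depends on the assumed number of grade 1 visits, on a false 0 appearing on both scales at once, and on sites applying the stopping clauses rather than Table 2. If sites follow Table 2, the loss of primary events is nil. The documents give no basis for saying that the loss would differ between arms. The defect is worth correcting because the correction is simple, not because a large bias has been shown.

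**What to change.** These changes concern assessment only, not treatment.

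1. In 2.4.1 and 2.4.2, state that a grade 0 reading during radiotherapy never ends assessment.
2. In 2.4.2, define recovery as grade 0 on both RTOG and WHO scales after completion of radiotherapy, in a participant with a previously recorded grade of 1 or more.
3. Report participants who never reached grade 1 as 'no RIOM', not as recovered.
4. Reconcile 2.4.1 and 2.4.2 with 2.5, Table 2, 4.1 and 6.5, so that sites have one instruction on how long assessment lasts.

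A confirmatory visit should not be made mandatory. Table 2 has no RTOG assessment at W9–W12 and follow-up after radiotherapy is by telephone, so a grade 0 at W8 could be confirmed on both scales only at W13 unless visits were added. If confirmation is wanted, limit it to visits where both scales are already scheduled.

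The cost is a few sentences in the protocol and case record form instructions, plus a few more weekly assessments during radiotherapy that Table 2 already schedules. No extra participants are needed. Because enrolment has begun, the change would go through the amendment and ethics approval route in section 6.2.

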#### Adherence strategies

2.4.3

Adherence to the intervention and maintenance of oral hygiene will be monitored throughout the treatment period by the staff nurse, oral hygiene coordinator, and study investigators. Family caregivers will be trained during the radiotherapy hospital stay to supervise intervention use and support oral hygiene practices following discharge. Intervention adherence will be documented using a drug compliance form, filled by the investigators during the hospital stay and by caregivers during the 6-week post-radiotherapy follow-up period. During the post-radiotherapy period, compliance will be assessed through telephonic follow-up and by verification of the remaining quantity of dispensed medicine packs at each follow-up visit.

#### Concomitant care

2.4.4

Concomitant medications considered by the Principal Investigator not to interfere with the efficacy or safety evaluation of the investigational Siddha regimen will be permitted during the study. Participants on stable doses of antihypertensive, antidiabetic, antiepileptic, or cardiac medications may continue their treatment as per standard clinical practice. In the intervention arm, clinically indicated supportive medications, including oral and topical analgesics and anti-inflammatory agents, may be administered to alleviate symptoms and improve patient comfort. All such medications will be prescribed based on the investigator's clinical judgment and in accordance with standard treatment practices. The use of these supportive medications will be appropriately documented.

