### Statistical methods

4.5

Baseline demographic and clinical characteristics of the participants will be summarised using descriptive statistical methods. Categorical data will be presented as frequencies and percentages, whereas continuous data will be expressed either as mean ± standard deviation or as median with interquartile range, based on the distribution of the data.

The primary outcome of the study, namely the severity of oral mucositis assessed using RTOG and WHO oral mucositis scales, will be analysed by comparing the proportion of participants who develop grade ≥2 mucositis in the two study groups. Depending on the suitability of the data, either the chi-square test or Fisher's exact test will be used for comparison. In addition, weekly mucositis grade distributions will be analysed to observe changes in severity, recovery patterns, and overall trends during treatment and follow-up.

For secondary outcomes, pain intensity measured using VAS will be compared between the groups at each assessment point using either the independent samples t-test or the Mann–Whitney U test, based on the data distribution. Analgesic use, categorised according to WHO three-step analgesic ladder, will be analysed as categorical data and compared between groups using the chi-square test or Fisher's exact test. Rescue medication use will be analyzed as a secondary outcome to compare overall analgesic requirements between the study groups. Laboratory investigations will be summarised descriptively and assessed for safety through appropriate within-group and between-group analyses.

The distribution of continuous variables will be checked using histograms to determine normality. Depending on the nature of the data, either parametric or non-parametric statistical methods will be applied for between-group comparisons. Subgroup analyses based on cancer treatment modalities will also be carried out to explore whether the treatment effects remain consistent across clinically relevant subgroups. However, these analyses will be considered exploratory in nature.

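### Discretionary analgesics and anti-inflammatory agents are expressly permitted in the intervention arm only, while analgesic use is compared between arms; this risks unequal co-treatment, with bias of unknown direction

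*Protocol article*

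**What the plan says.** Section 2.4.4 (Concomitant care) opens with a permission that is not tied to an arm: "Concomitant medications considered by the Principal Investigator not to interfere with the efficacy or safety evaluation" of the Siddha regimen are allowed. It then turns to one arm: "In the intervention arm, clinically indicated supportive medications, including oral and topical analgesics and anti-inflammatory agents, may be administered to alleviate symptoms". Prescribing rests on the investigator's "clinical judgment and in accordance with standard treatment practices", and use is to be documented. No sentence says the same for Arm B.

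For the control arm, section 2.4.2 states: "Participants in Arm B will receive SOC alone for the management of RIOM, as described in the intervention arm". It adds: "Additional topical anaesthetic and anti-inflammatory gels will be provided for oral mucositis of grade ≥ 2", under the institutional protocol. Section 2.4.1 gives Arm A the same component on the same trigger: benzydamine "along with topical anaesthetics and anti-inflammatory gels in cases of oral mucositis of grade" 2 or higher. The defined standard of care is therefore the same in both arms. It contains benzydamine and the gels; oral analgesics are not part of it.

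The outcome and analysis sections treat analgesic use as something measured in everyone. Section 2.5 takes the percentage of participants needing analgesics, by WHO ladder step, as a secondary outcome. Section 4.1 documents all analgesic use with its indication. Section 4.5 says: "Rescue medication use will be analyzed as a secondary outcome to compare overall analgesic requirements between the study groups".

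**The concern.** An arm-specific permission for a co-treatment matters most when that co-treatment is also an outcome, and here it is. If a site follows section 2.4.4 literally, Arm A has an express and discretionary route to analgesics and anti-inflammatory agents, while Arm B has to rely on the general clause.

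Three kinds of outcome are exposed:

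- **VAS pain**, which analgesia lowers.
- **Ladder step and rescue use**, which prescribing determines directly.
- **RTOG grade**, because Table 3 describes grade 1 partly by pain that needs no analgesic, grade 2 by pain that needs one, and grade 3 by pain that needs a narcotic. The grade 3 threshold in section 2.5 and the grade 2 threshold in section 4.5 both fall on these descriptors.

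A difference between arms on any of these could then reflect the prescribing rule as well as the Siddha regimen.

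**Working it through.** The point rests on wording, and no figure in the protocol tests it. I therefore set the passages side by side and added one illustration of scale.

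**Step 1. What each arm is expressly given**

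| Item | Arm A | Arm B |
|---|---|---|
| Benzydamine rinse | Yes (2.4.1) | Yes, same standard of care (2.4.2) |
| Topical anaesthetic and anti-inflammatory gels from grade 2 | Yes (2.4.1) | Yes (2.4.2) |
| General concomitant-medication clause | Applies (2.4.4) | Applies (2.4.4) |
| Discretionary oral and topical analgesics and anti-inflammatory agents | Expressly permitted (2.4.4) | No statement |

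Only the last row differs.

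**Step 2. Whether the general clause closes the gap.** It admits drugs that the Principal Investigator considers not to interfere with the efficacy evaluation. Table 2 lists VAS and the analgesic ladder under efficacy assessment. The Discussion accepts that supportive medication may affect symptom severity and outcome assessment. Analgesics in Arm B are therefore not barred, but they do not clearly pass the clause either. In Arm A the question does not arise.

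**Step 3. Consistency with the outcomes.** Sections 1.3, 2.5, 4.1 and 4.5 measure or compare analgesic or rescue use across both groups, and section 4.3 records rescue medication without an arm limit. These sections presuppose analgesic access in both arms, but section 2.4.4 states it for one.

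**Step 4. The gel provision.** Sections 2.4.1 and 2.4.2 tie the gels to grade 2 or higher. The Arm A sentence in section 2.4.4 also covers topical agents and is silent on grade. That leaves the relation between the two unclear; it is an ambiguity, not a direct contradiction.

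**Step 5. Protection from blinding.** Section 3.4 says treatment cannot be blinded, and that assessors are separate from allocation and administration and unaware of the group. This protects the grading. It does not act on what is prescribed before the grading.

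**Step 6. Illustration of scale (assumed shifts).** Inputs: a severe-mucositis rate of 43.6% under benzydamine (section 2.7), taken as true in both arms with no drug effect; 64 or 80 per arm (section 2.7); two-sided 5%. Let unequal co-treatment move the observed Arm A rate by x, so that p_A = 0.436 + x, and let p̄ be the mean of the two rates.

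- SE0 = √[2·p̄(1−p̄)/n]
- SE1 = √[(0.436·0.564 + p_A(1−p_A))/n]
- Rejection rate = Φ[(−1.96·SE0 − x)/SE1] + 1 − Φ[(1.96·SE0 − x)/SE1]

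For n = 80 and x = −0.05: p_A = 0.386, p̄ = 0.411, SE0 = 0.0778, SE1 = 0.0777. The two terms are Φ(−1.32) = 0.094 and 1 − Φ(2.61) = 0.005, about 0.098 in total.

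| Assumed shift in Arm A | 64 per arm | 80 per arm |
|---|---|---|
| −10 points | 21.2% | 25.4% |
| −5 points | 8.8% | 9.8% |
| −2 points | 5.6% | 5.7% |
| +2 points | 5.6% | 5.7% |
| +5 points | 8.7% | 9.7% |
| +10 points | 20.4% | 24.3% |

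The nominal rate is 5%. The shifts are mine; the protocol gives neither a size nor a sign.

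**The case against.** The best defence is that section 2.4.4 is loosely drafted and that both arms were meant to have the same access. Nothing prohibits analgesics in Arm B. The general clause is not limited by arm, and the outcome, data-management and analysis sections make most sense if control participants can receive analgesics. The Arm A sentence may only confirm that participants on the Siddha regimen are not denied conventional relief. The full or institutional protocol may settle the matter, and the Discussion already names supportive medication as a possible influence on outcomes.

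Much of this stands, and it rules out several stronger readings that a reader might infer:

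- **That Arm B gets only gels.** It also gets benzydamine, and the gel provision is the same in both arms.
- **That analgesics are withheld from Arm B.** No passage says so.
- **That the trial is already biased, or biased towards the Siddha regimen.** The text shows a risk. Freer analgesia may lower VAS scores, but it raises the ladder step and may raise the RTOG grade where that grade counts analgesic need. RTOG grades 2 to 4 also have mucosal descriptors that prescribing does not change.
- **That a handful of participants could account for the whole planned effect.** A 15% relative reduction on 43.6% is 0.15 × 43.6 = 6.5 points, but no passage says that co-treatment would move the grade of any given number of participants.

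The defence does not remove the arm-specific sentence. This is not a detail left out in condensing the protocol: the article states a rule and names one arm. Recording the use lets an imbalance be described, but does not undo it.

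**Conclusion.** The concern holds as an internal inconsistency that creates a risk of performance bias. The express permission for discretionary analgesics and anti-inflammatory agents names Arm A alone, while the outcomes and analyses treat analgesic and rescue use as comparable between arms. The risk extends to the primary outcome because the RTOG grades used are partly defined by analgesic need. Size and direction cannot be derived from the documents. The illustration shows only that, under an assumed common rate of 43.6%, a 2-point shift would hardly matter, whereas a 10-point shift would bring the two-sided rejection rate to between 20% and 25%.

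The conclusion assumes that sites follow section 2.4.4 as written. If the full protocol already gives Arm B the same permission, what remains is an error of wording in the article.

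**What to change.** Reconcile section 2.4.4 with sections 2.4.1, 2.4.2, 2.5, 4.1 and 4.5. State one supportive-medication rule that applies identically to both arms, with the same permitted classes, the same condition for use and the same documentation, and say how it relates to the gel provision from grade 2. Which rule that is should be decided by the sponsor's clinicians; the statistical requirement is only that it does not differ by arm.

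The cost is a short amendment, submitted to the ethics committee as section 6.2 requires, and a reminder to site staff. No new data are needed: section 4.1 already records all analgesic use with its indication, and section 4.3 already records concomitant and rescue medication. Enrolment has begun, and differences in prescribing cannot be reversed at analysis, so the change is best made now.
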